## Abstract

**Background:** Pathogenic variants in the Leucine-rich repeat kinase 2 (*LRRK2)* gene are the most common known monogenic cause of Parkinson's disease (PD). *LRRK2*-linked PD is clinically indistinguishable from idiopathic PD and inherited in an autosomal dominant fashion with reduced penetrance and variable expressivity that differ across ethnicities and geographic regions.

**Objective:** To systematically assess clinical signs and symptoms including non-motor features, comorbidities, medication and environmental factors in PD patients, unaffected *LRRK2* pathogenic variant carriers, and controls. A further focus is to enable the investigation of modifiers of penetrance and expressivity of *LRRK2* pathogenic variants using genetic and environmental data.

**Methods:** Eligible participants are invited for a personal or online examination which comprises completion of a detailed eCRF and collection of blood samples (to obtain DNA, RNA, serum/plasma, immune cells), urine as well as household dust. We plan to enroll 1,000 participants internationally: 300 with *LRRK2*-linked PD, 200 with *LRRK2* pathogenic variants but without PD, 100 PD patients with pathogenic variants in the *GBA* or *PRKN* genes, 200 patients with idiopathic PD, and 200 healthy persons without pathogenic variants.

**Results:** The eCRF consists of an investigator-rated (1 h) and a self-rated (1.5 h) part. The first part includes the Movement Disorder Society Unified Parkinson's Disease Rating, Hoehn &Yahr, and Schwab & England Scales, the Brief Smell Identification Test, and Montreal Cognitive Assessment. The self-rating part consists of a PD risk factor, food frequency, autonomic dysfunction, and quality of life questionnaires, the Pittsburgh Sleep Quality Inventory, and the Epworth Sleepiness as well as the Hospital Anxiety and Depression Scales. The first 15 centers have been initiated and the first 150 participants enrolled (as of March 25th, 2021).

**Conclusions:** LIPAD is a large-scale international scientific effort focusing on deep phenotyping of *LRRK2*-linked PD and healthy pathogenic variant carriers, including the comparison with additional relatively frequent genetic forms of PD, with a future perspective to identify genetic and environmental modifiers of penetrance and expressivity

**Clinical Trial Registration:**ClinicalTrials.gov, NCT04214509.

## Introduction

Pathogenic variants in the Leucine-rich repeat kinase 2 (*LRRK2*) gene are the most common known monogenic cause of Parkinson's disease (PD). First identified in 2004, *LRRK2* pathogenic variants account for up to ~40% of all PD cases in selected populations, e.g., North African Berber (1). In the PD phenotype-genotype database MDSGene (www.mdsgene.org), ~700 individual *LRRK2* pathogenic variant carriers are listed, but clinical information apart from cardinal signs of PD is overall scarce (1).

The majority of the reported *LRRK2* pathogenic variant-positive PD patients are of European descent (63%), whereas all other ethnicities comprise ~10% or fewer patients of described pathogenic variant carriers despite clusters in the Ashkenazi Jewish (AJ) and Arab Berber populations (1, 2). Definitely pathogenic variants identified in *LRRK2* include p.G2019S, p.R1441C/G/H, p.N1437H, p.Y1699C, and, p.I2020T. Of these, the p.G2019S pathogenic variant is the most common with an estimated frequency of 1% in sporadic and 4% in hereditary PD cases worldwide (3). However, data on many populations are still missing.

*LRRK2*-linked PD is inherited in an autosomal dominant fashion with reduced, age-dependent penetrance and variable expressivity that differ across ethnicities and geographic regions, indicating that ancestral background or environmental factors contribute to the manifestation and expressivity of pathogenic *LRRK2* variants. For example, at the age of 60 years, 60% of Tunisian p.G2019S pathogenic variant carriers manifest PD, compared with only 20% of the Norwegian carriers of the same pathogenic variant (4). Recent studies have suggested mitochondrial involvement in the penetrance of *LRRK2*-linked PD (5, 6). Environmental factors can also influence penetrance, as recently found in the Tunisian Arab Berber population, where tobacco and black tea use delayed age at onset in *LRRK2* pathogenic variant carriers (7).

*LRRK2*-linked PD is clinically indistinguishable from idiopathic PD, i.e., PD of unknown cause, although the disease course appears to be milder with regard to motor and cognitive functions (8). In this comparatively small subgroup of PD patients with a known etiology, valuable clues can be garnered toward pathophysiological mechanisms and targeted treatments, which may be generalized to idiopathic PD. Currently, there are three substances in clinical trial specifically targeting *LRRK2*: the LRRK2 kinase inhibitors DNL151 (NCT04557800) and DNL201 (NCT04551534) from Denali and the antisense oligonucleotide BIIB094 (NCT03976349) from Biogen (2). However, no genetic testing guidelines and no clinical trial-ready cohorts exist to date.

To identify *LRRK2* pathogenic variant carriers among 10,000 PD patients from 15 countries and to establish a clinical trial-ready cohort, the ROPAD study was initiated (9). The ROPAD study performs genetic testing of pathogenic variants in the *LRRK2* and *GBA* genes and, if negative, carries out genetic screening of 68 genes linked to PD or related movement disorders. Out of the first 1,288 participants who underwent genetic testing in ROPAD, 40 (3.1%) harbored pathogenic or likely pathogenic *LRRK2* variants, 109 (8.5%) harbored *GBA* variants, three (0.2%) had alterations in both genes (9). The ROPAD study is still ongoing and continues to identify *LRRK2* pathogenic variant carriers internationally. It gathers only basic clinical data: age at examination, age at onset, cardinal PD symptoms, and 12/33 items of MDS-UPDRS Part III and, thus, does not allow a systematic in-depth characterization of *LRRK2* pathogenic variant carriers.

Recently published data from the currently largest multinational prospective study that includes *LRRK2* pathogenic variant carriers, i.e., the Parkinson's Progression Markers Initiative (PPMI), provide more phenotypic details on *LRRK2* pathogenic variant carriers across international sites (6). However, as the focus of the PPMI study is predominantly on biomarkers, it does not cover environmental factors in-depth, and only includes participants with a PD diagnosis 2 years or less before enrolment who are untreated with PD medication. There remains a gap in combining phenotypic, genetic, and environmental data on *LRRK2* pathogenic variant carriers internationally, regardless of the onset of signs and symptoms and their medication status, that LIPAD is aiming to close. The objectives of the LIPAD study are (1) to provide a systematic characterization of PD patients and unaffected carriers with pathogenic variants in the *LRRK2* gene; and (2) to enable the investigation of modifiers of penetrance of *LRRK2* pathogenic variants using genetic and environmental data.

Here, we describe a protocol and a feasibility study of the first 150 participants and give a brief overview of nested studies within LIPAD. Of note, the LIPAD protocol has also been adapted to take place online due to COVID19 contact restriction measures.

## Patients and Methods

### General Setting

We aim to build the LIPAD cohort consisting of 1,000 participants internationally: 300 of them with *LRRK2*-PD (*LRRK2*+/PD+), 200 with pathogenic *LRRK2* variants but without PD (*LRRK2*+/PD-), 100 PD patients with pathogenic variants in PD genes other than *LRRK2* (genPD), 200 patients with idiopathic PD from the same populations (iPD; *LRRK2*-/PD+), and 200 healthy persons without pathogenic variants (HC). The majority of participants will be enrolled after genetic analysis within ROPAD (Figure 1). Extrapolating from the ROPAD findings, we expect to have a sufficient number of participants in the *LRRK2*+/ PD+, iPD, and genPD groups. Further, family members of pathogenic *LRRK2* variant carriers will be asked to participate in the LIPAD study and will be genetically tested for the familial pathogenic *LRRK2* variant. Depending on the results, they will be assigned either to *LRRK2*+/PD- or HC group. Healthy persons without pathogenic variants will be recruited from spouses of study participants or the general population. Within an anticipated 24-month recruitment period per site, ~25 centers in 10 countries on three continents will be established. Each center will have 24 months for recruitment after initiation. The majority of the centers will be those already participating in ROPAD, however, additional centers that do not participate in ROPAD but follow *LRRK2* pathogenic variant carriers will be invited to become LIPAD sites.

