## Results

A comprehensive eCRF has been developed, consisting of an investigator-rated (1 h) and a self-rated (1.5-h) part. The questionnaires are listed in Table 1. We used validated versions of questionnaires and scales in the local languages.

**Table 1 T1:** Content of the LIPAD electronic case report form.

Demographic and general data	Genetic result, age, gender, years of education, the highest level of education, handedness, medication/treatment, medical history, family history concerning PD
PD criteria	MDS clinical diagnostic criteria for PD, absolute exclusion criteria, red flags
Clinical scores	MDS-UPDRS (Movement Disorder Society – Unified Parkinson's Disease Rating Scale) Hoehn & Yahr scale Schwab & England scale Brief smell identification test (BSIT) Montreal Cognitive Assessment (MoCA)
The self-rating part	PD risk factor questionnaire (PD-RFQ-U) Food frequency questionnaire Autonomic dysfunction (SCOPA-AUT) WHO Quality of life questionnaire (WHO-QoL) Pittsburgh Sleep Quality Inventory Epworth Sleepiness Scale Hospital Anxiety and Depression Scales

The first 10 centers across Germany and five international sites have been initiated with further centers currently undergoing ethical review (Figure 2). The first 150 participants have been enrolled (as of March 25th, 2021); Table 2.

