**Figure 2 F2:**
[figure not shown]
International centers participating in LIPAD. In blue: centers with ethics approval; in black: centers in the process of receiving ethics approval.

**Table 2 T2:** Exemplary demographic and clinical characteristics of the first 150 enrolled LIPAD participants.

	***LRRK2*** **+/PD+ (group 1)**	***LRRK2*** **+/PD-(group 2)**	**iPD;LRRK-/ PD+ (group 3)**	**genPD (group 4)**	**HC (group 5)**
	***N*** **= 7**	***N*** **= 1**	***N*** **= 115**	***N*** **= 25**	***N*** **= 2**
Sex (male), *n* (%)	2 (28.6%)	0	64 (55.7%)	15 (60%)	2 (100%)
Age, mean (±SD)	60.6 (± 9.2)	40	63.3 (± 10.8)	56.4 (± 11.6)	57 (± 12)
Family history of PD, *n* (%)	3 (42.9%)	1 (100%)	19 (16.5%)	7 (28%)	1 (50%)
MDS-UPDRSIII, mean	37.7 (± 20.3)	0	34.3 (± 14.4)	28.6 (± 12.5)	4 (± 4)
(±SD), *n* complete	*N* = 3	*N* = 1	*N* = 59	*N* = 11	*N* = 2
H&Y, mean (±SD)	3 (± 0.6)	0	2.1 (± 0.6)	2.1 (± 0.7)	0.5 (± 0.5)
Schwab & England Scale, mean (±SD)	71.7 (± 21.1)	-	81.9 (± 14.7)	84.4 (± 11.2)	100 (± 0)
MoCA, mean (±SD)	25.8 (± 3.3)	29	26.6 (± 3.3)	27.6 (± 2.1)	26.5 (± 1.5)
BSIT, mean (±SD)	6.2 (± 1.7)	11	6 (± 2.6)	6.5 (± 3.3)	11 (± 1)

*H&Y, Hoehn and Yahr; MoCA, Montreal Cognitive Assessment; BSIT, Brief Smell Identification Test*.

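### Idiopathic PD enrolment runs far ahead of LRRK2+/PD+ enrolment (57.5% against 2.3% of target), and the stated tests do not protect the comparison from confounding by country or site

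*Protocol article*

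**What the plan says.** In the protocol article, General Setting sets the group sizes. The two that matter here are "300 of them with *LRRK2*-PD" and "200 patients with idiopathic PD from the same populations". Most participants are to come through ROPAD, the genetic screening study. The plan is that about "25 centers in 10 countries on three continents will be established", each with its own 24-month window. Centers outside ROPAD that follow LRRK2 carriers will also be invited.

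Results reports that "The first 10 centers across Germany and five international sites have been initiated". Table 2, titled "Exemplary demographic and clinical characteristics of the first 150 enrolled LIPAD participants", gives 7 LRRK2+/PD+, 1 LRRK2+/PD-, 115 idiopathic PD, 25 other genetic PD and 2 healthy controls. It has no split by country, site or mode of examination.

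Data Analysis plans raw and corrected frequencies, naming sex, disease duration and medication as examples of influencing factors. The groups are then compared with t-tests and chi-square tests at the 0.05 level.

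**The concern.** Drawing the idiopathic comparators from the populations that supply the LRRK2-PD patients is a stated feature of the design. It is there so that a difference between the groups can be read as a difference by genotype. The counts show the two groups filling at very different speeds while the site network is still growing. If the idiopathic places are largely used up at the centers that opened first, and many LRRK2-PD patients arrive later from other countries, genotype becomes mixed up with country, site and calendar time.

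The article itself says why geography matters. The Introduction states that penetrance and expressivity of LRRK2 variants vary across ethnic groups and regions. Its example is 60% against 20% penetrance at age 60 in Tunisian and Norwegian carriers of the same variant. Yet the comparison in Data Analysis is stated as simple two-sample and contingency-table tests, and neither country nor site is among the named factors. Later adjustment cannot recover a comparison at a site that has LRRK2-PD patients but no idiopathic patients, so pacing matters as well as the model.

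**Working it through.** **Inputs.** Targets (General Setting): 300 + 200 + 100 + 200 + 200 = 1,000, which reproduces the stated total. Enrolled (Table 2): 7 + 1 + 115 + 25 + 2 = 150, which also agrees.

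**Fill and mix so far.**

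| Group | Enrolled / target | Fill | Share of enrolled | Planned share |
|---|---|---|---|---|
| LRRK2+/PD+ | 7/300 | 2.3% | 4.7% | 30% |
| Idiopathic PD | 115/200 | 57.5% | 76.7% | 20% |
| Healthy controls | 2/200 | 1.0% | 1.3% | 20% |

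**Is the skew only early noise?** In ROPAD, 40 of 1,288 patients (3.1%) carried an LRRK2 variant. Among the PD patients enrolled in LIPAD (7 + 115 + 25 = 147), 7/147 = 4.8% do (95% CI 2.3% to 9.5%). This is compatible with the ROPAD yield and shows no clear enrichment for carriers. The skew is what the main recruitment route would be expected to produce without pacing.

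**Projection, assuming that the mix stays as it is.**
- Total enrolled when idiopathic PD reaches 200: 200 / (115/150) = 261.
- LRRK2+/PD+ at that point: 7 + 85 × 7/115 = 12.2.
- Range: the exact 95% CI for 7/122 is 2.34% to 11.46%. With p as that proportion, the carriers added alongside 85 idiopathic patients are 85 × p/(1 − p), or 2.0 to 11.0. Adding the 7 already enrolled gives 9 to 18. This reflects uncertainty in the mix only.
- Carrier target still outstanding: (300 − 18)/300 = 94% to (300 − 9)/300 = 97%.

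**Ratio needed for both groups to fill together.** Remaining places are 300 − 7 = 293 and 200 − 115 = 85. That is 293/85 = 3.4 LRRK2-PD patients per idiopathic patient, against 7/115 = 0.06 so far. Seen the other way, 85/293 = 0.29 idiopathic patients per LRRK2-PD patient, or about 2 per 7.

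**Why not the overall target ratio of 2 per 3?** At that rate the 85 places would last for 85 × 3/2 = 127.5, or about 128, LRRK2-PD patients. About 293 − 128 = 165 would then have no concurrent comparator.

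**The case against.** A reader might infer that the idiopathic group will close before the LRRK2-PD patients are recruited, and that it will not come from the same populations. The documents support neither statement. The 200 is a target with no closing rule attached. Table 2 does not say where the 115 were enrolled, and 10 German centers out of 15 says nothing about participants per center. Nor does the article say that the remaining LRRK2-PD patients must come mainly from later international sites. The 85 open places could be used at later sites, and more LRRK2-PD patients could come from sites already open.

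The projection also rests on 7 patients, at an early stage affected by the pandemic and before all the planned centers had opened. The sex difference in Table 2 (2/7 against 64/115 male) should not be used as evidence of imbalance: Fisher's exact p is 0.25, and the exact 95% CI for 2/7 is 4% to 71%. Confounding by online or on-site examination cannot be judged either, because mode is not reported by group.

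Finally, a condensed article may leave quotas and pacing to the full protocol, so the absence of a pacing rule here is not in itself a fault. The penetrance objective concerns carriers and does not need the idiopathic group.

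All of this stands, and it limits the point to a risk. What remains is what the article does state: a commitment to common populations, counts showing that no effective pacing towards 300:200 was operating in the first 150, and comparison tests that leave out the geographic factors which the Introduction describes as important.

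**Conclusion.** The point holds as a risk to the comparison of LRRK2-PD with idiopathic PD, and not as a demonstrated contradiction. The fill fractions of 57.5% and 2.3% are exact. On the assumption of an unchanged mix, the idiopathic target is met at about 261 enrolments with about 12 LRRK2-PD patients (9 to 18), leaving 94% to 97% of their target to come. Whether this confounds genotype with country, site or calendar time depends on where both groups are enrolled, which the article does not report. The stated t-tests and chi-square tests would not protect against it if it occurred. If the full protocol already contains a pacing or matching rule, the sponsor should state it and explain how 115 to 7 arose under it.

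**What to change.** 1. **Pacing.** Hold the remaining 85 idiopathic places. Release them by country or site in proportion to LRRK2-PD patients newly enrolled there, at about 85:293 (roughly 2 per 7). Frequency-match on age band and sex where feasible. This is practicable because participants are generally invited after genetic screening. Do not apply the rule to healthy controls, who stand at 2 of 200 and would only be held back further.

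2. **Analysis.** Replace the plain t-tests and chi-square tests for LRRK2-PD against idiopathic PD with models stratified by or adjusted for country or site, age, sex and disease duration. Add a sensitivity analysis restricted to countries or sites that contribute both groups. Report both groups by country or site.

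**Cost.** A recruitment instruction to sites and a change to the analysis text. Early sites pause idiopathic enrolment, and total accrual will look slower. The adjusted analysis may lose some precision, more so if few further LRRK2-PD patients come from the sites that enrolled the 115. No extra patients are needed.

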**Figure 1 F1:**
[figure not shown]
Paths of enrolment into the LIPAD study. *LRRK2*+/PD+: PD patients carrying a pathogenic LRRK2 variant, *LRRK2*+/PD-: unaffected carriers of pathogenic *LRRK2* variants, genPD: PD patients with pathogenic variants in PD genes other than *LRRK2, iPD; LRRK2-/PD*+*:* patients with idiopathic PD from the same populations, HC: healthy persons without pathogenic variants.

### Inclusion Criteria

Recruited participants have to meet one of the following criteria: (i) clinical diagnosis of PD according to the Movement disorder Society (MDS) diagnostic criteria, (ii) first- or second-degree relative of a participant that is positive for a pathogenetic *LRRK2* variant, (iii) healthy participants with or without a family history of PD in a control group. All participants have to be above 18 years of age and have to sign an informed consent form.

Participants with the following *LRRK2* variants will be included in the *LRRK2*+ group: p.Gly2019Ser (c.6055G>A), p.Arg1441His (c.4322G>A), p.Arg1441Cys (c.4321C>T), p.Arg1441Gly (c.4321C>G), p.Asn1437His (c.4309A>C), p.Ile2020Thr (c.6059T>C), p.Tyr1699Cys (c.5096A>G).

### Study Design

Upon completion of genetic screening (e.g., in ROPAD), participants are invited for a personal examination using the three-level biomaterial protocol. During a single visit, an electronic Case Report Form (eCRF) is administered and blood samples for DNA, RNA, serum/plasma, immune cell isolation, urine, and household dust for toxicological analyses are collected.

The three-level protocol was designed to accommodate available laboratory facilities at the different sites. The details of the three levels for biomaterial sampling are listed in Supporting Information Methods S2 in Supplementary Material.

In case genetic testing has not been performed before, a dried blood spot card will be sent for DNA extraction and genetic screening, as specified in ROPAD.

There are no serious safety concerns associated with the study. Participants may experience temporary discomfort during venous blood sampling and while answering the questions. However, they are instructed that they are free to omit questions they would rather not answer. There are no health risks associated with the collection of urine and house dust.

### Data Analysis

Data analysis will be performed at the Institute of Neurogenetics (University of Luebeck, Germany). To cover the first objective, which is the systematic characterization of PD patients and unaffected carriers with pathogenic variants in the *LRRK2* gene, we will describe the frequency of all clinical signs and symptoms including non-motor signs and the most important influencing factors such as sex, disease duration, and medication. This will result in raw and corrected frequencies with 95% confidence intervals. We will use t-tests for numerical and continuous variables and chi-square tests for categorical variables at a significance level of 0.05 for the comparisons of the clinical signs and symptoms across the groups.

For aim 2, which is to investigate the modifiers of penetrance of pathogenic *LRRK2* variants using genetic and environmental data, we will examine penetrance in logistic regression models to quantify the influence of different factors impacting penetrance.

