## Discussion

LIPAD is a large-scale international scientific effort focusing on deep phenotyping of *LRRK2*-linked PD and healthy pathogenic variant carriers, including a comparison with additional relatively frequent genetic forms of PD, and with a future perspective to identify genetic and environmental modifiers of penetrance and expressivity.

The clinical assessment in LIPAD is close to the one used in the currently largest multinational cohort of genetic PD (PPMI), except for lack of collection of cerebrospinal fluid, but with the addition of an extensive questionnaire on environmental factors (15). Further, there are no restrictions on the age at diagnosis or medication for inclusion in the LIPAD study. Several other multinational prospective studies focusing on pathogenic *LRRK2* variants included only a small number of populations (4, 16, 17), revealing an important knowledge gap in multinational, standardized, genetic prospective studies, which LIPAD is aiming to close.

A comprehensive investigation of modifiers of penetrance and expressivity requires assessment of a considerable number of pathogenic variant carriers. Due to the direct enrolment of family members at an international scale, the LIPAD study will enable the analysis of modifiers of penetrance in different populations in one setting. Our recruitment strategy, mainly through the international multicenter ROPAD study, will ensure participation of a large number of *LRRK2*+/PD+ patients.

With the nested studies, which will be conducted on a subset of participants, we are aiming to provide a more in-depth phenotypic characterization especially of non-affected carriers of *LRRK2* pathogenic variants.

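### The t-tests and chi-square tests named for group comparisons assume independent participants, but relatives of LRRK2 carriers, and possibly spouses, are enrolled by design in LRRK2+/PD- and HC

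*Protocol article*

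**What the plan says.** **Recruitment.** Under General Setting, "family members of pathogenic *LRRK2* variant carriers will be asked to participate in the LIPAD study". These relatives are tested for the familial variant and placed in LRRK2+/PD- or HC according to the result. The Inclusion Criteria list as one route of entry a "first- or second-degree relative of a participant that is positive for a pathogenetic *LRRK2* variant". General Setting adds: "Healthy persons without pathogenic variants will be recruited from spouses of study participants or the general population". The split between spouses and the general population is not given. The Discussion presents family enrolment as a strength: "Due to the direct enrolment of family members at an international scale, the LIPAD study will enable the analysis of modifiers of penetrance".

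**Targets (General Setting).** 300 LRRK2+/PD+, 200 LRRK2+/PD-, 100 genPD, 200 iPD and 200 HC, which add up to the stated 1,000.

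**Analysis (Data Analysis).** For objective 1: "This will result in raw and corrected frequencies with 95% confidence intervals". Clinical signs and symptoms are then compared across groups with t-tests for measured variables and chi-square tests for categorical ones, at the 0.05 level. For aim 2, penetrance is examined with logistic regression. Family, household, kinship, clustering and matching are not mentioned in any of this.

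**The concern.** The recruitment plan and the named tests do not fit together. Relatives share genetic background, and relatives and spouses often share a home and habits, so their outcomes and exposures tend to be correlated. Standard t-tests and chi-square tests treat each participant as a separate, independent piece of information.

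Two effects follow, and they pull in opposite directions:

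- **Several relatives in the same group.** The group carries less information than its head count suggests, so p-values are too small.
- **Relatives or spouses on opposite sides of a comparison.** The shared component cancels in the difference, so the unpaired test overstates the standard error and loses power.

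Which effect prevails varies from contrast to contrast, so a reader of the results could not apply a single mental correction. LRRK2+/PD- is central to both objectives, and its main described source is the families of carriers.

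**Working it through.** The article states no power, interval width, family size or correlation, so there is no statistical figure of its own to reproduce.

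**Inputs from the article:** the group sizes above, alpha 0.05 and 95% intervals. Two-sided testing is assumed, since sidedness is not stated.

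**Assumptions not in the article:** m = 2 to 4 unaffected carriers per family (m = 1 for the one-relative case) and intra-family correlation ICC (r for pairs) from 0.1 to 0.5, taken to be the same within and across groups.

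**Formulas**
- Design effect within a group: DE = 1 + (m − 1) × ICC.
- Variance the test assumes: V0 = 1/n1 + 1/n2.
- True variance: V = 1/n1 + DE/n2 − 2 × r × pairs/(n1 × n2).
- Actual type I error: 2 × [1 − Φ(1.96/√(V/V0))].

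**1. 200 LRRK2+/PD- versus 200 unrelated iPD.** One group is clustered and there are no cross-group pairs, so V/V0 = (1 + DE)/2.

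| m | ICC | V/V0 | Actual level of a 5% test |
|---|---|---|---|
| 2 | 0.1 | 1.05 | 5.6% |
| 3 | 0.2 | 1.20 | 7.4% |
| 3 | 0.3 | 1.30 | 8.6% |
| 4 | 0.5 | 1.75 | 13.8% |

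**2. 300 LRRK2+/PD+ versus 200 LRRK2+/PD-.** Each unaffected carrier is assumed to have a related proband in the study (200 pairs). With one relative per proband and r = 0.3, V0 = 1/300 + 1/200 = 0.008333 and V = 0.008333 − 2 × 0.3 × 200/60,000 = 0.006333. The ratio is 0.76 and the level 2.5%. At r = 0.1 the level is 4.1%, and at r = 0.5 it is 1.1%. With 3 to 4 relatives per proband the same contrast turns liberal, at 5.5% to 11.0%. With 2 per proband the two effects nearly offset (4.8% to 3.9%).

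**3. 200 iPD versus 200 HC, in the extreme case that every HC is the spouse of an iPD participant.** V/V0 = 1 − r. The levels are 3.9%, 1.9% and 0.6% at r = 0.1, 0.3 and 0.5. If a quarter of HC are such spouses, they are 4.7%, 4.2% and 3.6%.

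**4. A 30% frequency in 200 LRRK2+/PD-, if the interval ignores families.** The naive half-width is 1.96 × √(0.3 × 0.7/200) = 6.35 points, and the correct one is 6.35 × √DE.

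| m | ICC | DE | Correct half-width (points) | Coverage of naive interval |
|---|---|---|---|---|
| 2 | 0.1 | 1.1 | 6.7 | 93.8% |
| 3 | 0.3 | 1.6 | 8.0 | 87.9% |
| 4 | 0.5 | 2.5 | 10.0 | 78.5% |

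**5. Penetrance model, if fitted as plain logistic regression.** This was simulated with 300 affected and 200 unaffected carriers, exposure correlation 0.5 within families and 1,500 runs per setting. A null exposure is declared significant in 1.0%, 4.4% and 12.3% of runs with 1, 2 and 4 relatives per proband. With family-clustered variance the figures are 4.1%, 5.6% and 5.9%.

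**The case against.** The strongest reply is that this is a journal article. Variance estimators and cluster terms are commonly left to the full protocol or analysis plan. That stands for three items:

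- The interval sentence names no method.
- Logistic regression leaves room for random effects, GEE or clustered variance.
- The one-line nested genome-wide analysis names no model.

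A reader might infer that every interval, test and model in the study treats participants as independent. The article does not say so. The reply does not cover the t-tests and chi-square tests, which are named outright and in standard form do not suit related participants.

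A reader might also put the type I error at 10% to 12% for families of three with correlation 0.2 to 0.3. That applies the full design effect (1.4 to 1.6) to both groups. The iPD group comes mainly through ROPAD as patients, not as relatives, and with only one of two equal groups clustered the figure is 7.4% to 8.6%.

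Three further points are fair:

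- Family size and correlation are not in the article, and at the low end the error is negligible.
- HC may come largely from the general population.
- No comparison of carriers with their non-carrier relatives is planned, so a loss of power for that contrast cannot be held against the plan.

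Finally, ignoring clustering distorts standard errors and leaves the raw frequencies as they are. Objective 1 is descriptive, which limits the damage.

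**Conclusion.** The point holds for the t-tests and chi-square tests in contrasts that involve LRRK2+/PD- or HC. The named tests do not fit a design that deliberately enrols relatives and may enrol spouses. Their true level can lie on either side of 5%: across the assumed scenarios for these tests, from about 0.6% to about 14%. The net direction for a given contrast depends on how many relatives each family contributes and how alike they are, which the article does not give. With 2 per family and ICC 0.1, the level is 4.8% to 5.6% for the carrier contrasts in steps 1 and 2. The comparison of iPD with genPD is largely unaffected, because both groups come mainly through ROPAD as patients.

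For the 95% intervals and the logistic models the article is silent rather than wrong. The calculations show what would follow if families were ignored there too. This should be corrected, but it does not invalidate the study.

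**What to change.** 1. Record a family/household ID for every participant at enrolment.
2. For contrasts involving LRRK2+/PD- or HC, replace the t-tests and chi-square tests with GEE, mixed models or cluster-robust equivalents, clustered on family/household.
3. State that the same family-clustered variance will be used for the 95% intervals of the frequencies and for the logistic penetrance models.

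The cost is one or two linkage fields, slightly more analysis work and some wider intervals. The timing is good: Table 2 shows 1 LRRK2+/PD- and 2 HC participants among the first 150, so links can still be captured prospectively. Reconstructing them later across about 25 centers would be harder.

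A kinship-based model for the genome-wide analysis and a separate family-stratified contrast are optional and not needed to repair this point.
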